### 7.3 LDCT

All the study subjects will undergo LDCT screening within six weeks of randomization. After the LDCT, the patient will be informed of the results by mail. If no further procedures are required, next LDCT will be scheduled for 1y +/- two months). With intermediate LDCT results, follow-up scan will be ordered at three months. With positive LDCT results, the patient will be referred to pulmonologist. After the second round LDCT, the subject is scheduled a study visit in which LDCT results are communicated to the subject. In the case of negative LDCT results, patient enter survival follow-up. With intermediate results, new LDCT will be ordered at 2 or 12months, and positive results will result in referral to pulmonologist. Nodule detection algorithm is presented in Figure 3.

Radiation exposure of single LDCT (effective dose) is 1.6-2.4 mSv, which corresponds to about ½-1v background radiation exposure. During its lifetime, humans are exposed to ionizing radiation from both

natural and artificial sources and the average effective dose received by Finns in 2018 is 5.9 mSv, of which about two thirds (4 mSv) is caused by radon. The additional risk caused by radiation from CT scans performed during the study, ie the risk of cancer, is low. Randomized evidence suggest that annual LDCT in the investigated population decreases lung cancer and all cause mortality and therefore benefits of LDCT clearly outweigh the potential harms.

#### 7.4 Biomarkers

The study subjects will undergo blood sampling for experimental biomarker analysis such as circulating tumor DNA at baseline and 1y.

#### 7.5 Lung cancer status and survival follow-up

The lung cancer status and stage at diagnosis will be followed during the intervention period. Furthermore, the status will be updated from electronic patients records and/or phone call up to 3y from randomization.

**Figure 3. Nodule detection algorithm (based on NELSON study protocol)**

| Screen round 1: baseline                                                                                                                                                                                                                                                                                                                                                                                                                                                                                                                                                                                                                                                                                                                                                                                                                                                                                                                                                                                                                                                                                                            |                               | Screen round 1: follow-up scan                |                        | Screen round 2-3                                           |                                | Screen round 4                                              |                                |
|-------------------------------------------------------------------------------------------------------------------------------------------------------------------------------------------------------------------------------------------------------------------------------------------------------------------------------------------------------------------------------------------------------------------------------------------------------------------------------------------------------------------------------------------------------------------------------------------------------------------------------------------------------------------------------------------------------------------------------------------------------------------------------------------------------------------------------------------------------------------------------------------------------------------------------------------------------------------------------------------------------------------------------------------------------------------------------------------------------------------------------------|-------------------------------|-----------------------------------------------|------------------------|------------------------------------------------------------|--------------------------------|-------------------------------------------------------------|--------------------------------|
| Screening result                                                                                                                                                                                                                                                                                                                                                                                                                                                                                                                                                                                                                                                                                                                                                                                                                                                                                                                                                                                                                                                                                                                    | Protocol                      | Screening result                              | Protocol               | Screening result                                           | Protocol                       | Screening result                                            | Protocol                       |
| NEGATIVE
- NODCAT I
- NODCAT II                                                                                                                                                                                                                                                                                                                                                                                                                                                                                                                                                                                                                                                                                                                                                                                                                                                                                                                                                                                                                                                                                        | Screening next round          | NEGATIVE
- GROWCAT A
- GROWCAT B | Screening next round   | NEGATIVE
- new and NODCAT I
- GROWCAT A       | Screening next round           | NEGATIVE
- NODCAT I
- NODCAT II
- GROWCAT A | End of screening               |
| INDETERMINATE
- NODCAT III                                                                                                                                                                                                                                                                                                                                                                                                                                                                                                                                                                                                                                                                                                                                                                                                                                                                                                                                                                                                                                                                                                | Follow-up scan after 3 months | POSITIVE
- GROWCAT C                | Referral pulmonologist | INDETERMINATE
- GROWCAT B
- new and NODCAT II | Follow-up scan after 12 months | INDETERMINATE
- GROWCAT B                         | Follow-up scan after 12 months |
| POSITIVE
- NODCAT IV                                                                                                                                                                                                                                                                                                                                                                                                                                                                                                                                                                                                                                                                                                                                                                                                                                                                                                                                                                                                                                                                                                      | Referral pulmonologist        |                                               |                        | INDETERMINATE
- new and NODCAT III               | Follow-up scan after 6-8 weeks | INDETERMINATE
- new and NODCAT III                | Follow-up scan after 6-8 weeks |
|                                                                                                                                                                                                                                                                                                                                                                                                                                                                                                                                                                                                                                                                                                                                                                                                                                                                                                                                                                                                                                                                                                                                     |                               |                                               |                        | POSITIVE
- GROWCAT C
- new and NODCAT IV      | Referral pulmonologist         | POSITIVE
- NODCAT IV
- GROWCAT C               | Referral pulmonologist         |
| NODULE CATEGORY based on volume
NODCAT I      nodule with benign characteristics, as fat/benign calcifications
NODCAT II      solid nodules with a volume of <50 mm 
pleural-based solid nodules with a minimal diameter of <5 mm
non-solid component partial solid nodule with a mean diameter of <8 mm
non-solid nodules with a mean diameter of <8 mm

NODCAT III      solid nodules with a volume of 50-500 mm 
pleural-based solid nodules with a minimal diameter of 5-10 mm
solid nodule with a non-solid component with a mean diameter of ≥8mm

NODCAT IV      solid nodules with a volume of >500 mm 
pleural-based solid nodule with a minimal diameter of >10 mm
solid component in a partial solid nodule with a volume of >500 mm 

NODULE CATEGORY based on volumedoublingtime (growth)
GROWCAT A      volumedoublingtime >600 dagen
GROWCAT B      volumedoublingtime 400-600 dagen
GROWCAT C      volumedoublingtime <400 dagen
new solid component in previously existing non-solid nodule |                               |                                               |                        |                                                            |                                |                                                             |                                |

At three and six months (+/- one month) after randomization, patient is called to evaluate whether they are active smokers and is they have quitted what is the date of smoking cessation.

The survival follow-up period can last up to 3 years from inclusion

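### Figure 3 gives no weight to a part-solid nodule's solid component between 50 and 500 mm³, so at baseline it can be negative where a solid nodule of the same volume is indeterminate

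*Protocol*

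**What the plan says.** Figure 3 of the protocol, which is said to be based on the NELSON protocol, sorts nodules into categories and ties each category to a screening result.

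- **Solid nodules** are graded by volume in mm³: "solid nodules with a volume of <50 mm" is NODCAT II, "solid nodules with a volume of 50-500 mm" is NODCAT III, and anything above 500 is NODCAT IV.
- **Part-solid nodules** have three lines. NODCAT II has "non-solid component partial solid nodule with a mean diameter of <8 mm", NODCAT III has "solid nodule with a non-solid component with a mean diameter of ≥8mm", and NODCAT IV has "solid component in a partial solid nodule with a volume of >500 mm" (cubic millimetres).
- **Baseline results:** "NEGATIVE - NODCAT I - NODCAT II" leads to the next screening round, "INDETERMINATE - NODCAT III" to a follow-up scan after 3 months, and "POSITIVE - NODCAT IV" to referral to a pulmonologist.
- **Growth lines:** GROWCAT C includes a solid component that newly appears in a nodule earlier seen as non-solid. It is a positive result.

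Section 7.3 puts the next-round scan at 1 year ± two months. Section 8 requires a letter giving the overall result and the next step. Section 15 says the protocol must be followed exactly. None of these places says which category applies when a nodule meets two.

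**The concern.** Figure 3 measures solid tissue by volume when the nodule is wholly solid. When the nodule is part-solid it ignores that volume until it passes 500 mm³. The same amount of solid tissue can then give a different baseline result and a different date for the next scan. The figure also treats solid tissue in a previously non-solid nodule as grounds for a positive result when it is new, but gives it no weight at baseline between 50 and 500 mm³.

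The category decides what the subject's letter says and when the subject is scanned again. It is also the test result behind sensitivity and positive predictive value (section 17.2.2) and specificity (section 17.2.3). An unreconciled classification can therefore affect both the handling of individual subjects and the accuracy endpoints.

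**Working it through.** The plan states no figure that could be reproduced here. The check sets the lines side by side and tests whether the affected nodules can exist.

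**1. The lines side by side, with baseline results**

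| Category | Solid nodule | Part-solid nodule | Baseline result |
|---|---|---|---|
| II | volume under 50 mm³ | non-solid component under 8 mm | negative, next round |
| III | volume 50–500 mm³ | non-solid component 8 mm or more | indeterminate, scan after 3 months |
| IV | volume over 500 mm³ | solid component over 500 mm³ | positive, referral |

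No part-solid line uses a solid component of 50–500 mm³.

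**2. Can such nodules exist?** Assume spheres: V = π·d³/6 and d = (6V/π)^(1/3).

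- d = 8 mm gives V = π × 512 / 6 = 268 mm³.
- V = 50 mm³ gives d = 4.57 mm.
- V = 500 mm³ gives d = 9.85 mm.

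The wording allows two readings of the 8 mm diameter.

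- *It spans the whole nodule.* The solid part must fit inside a sphere of less than 8 mm, so solid parts from 50 to just under 268 mm³ are NODCAT II. As a share of the band this is (268 − 50) / (500 − 50) = 218 / 450 = 48%. The upper end is a limit only, because a solid part that filled the sphere would leave no non-solid component.
- *It describes the non-solid part alone.* The whole range from 50 to 500 mm³ is open.

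**3. Worked example.** A solid part of 100 mm³ has d = 5.76 mm. It fits inside a 7 mm nodule (π × 343 / 6 = 180 mm³). The part-solid nodule is NODCAT II, hence negative at baseline. A solid nodule of 100 mm³ is NODCAT III, hence indeterminate.

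**4. Difference in timing at baseline.** The nominal gap is 12 − 3 = 9 months. With the ± 2-month window on the yearly scan, and the 3-month scan on time, it is 7 to 11 months.

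**5. Round 2.** A new NODCAT II nodule is indeterminate with a scan after 12 months. A new NODCAT III nodule is indeterminate with a scan after 6–8 weeks. The result is the same, and only the timing differs.

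**6. Solid component above 500 mm³.** Every part-solid nodule is already II or III by diameter, so one with a solid component above 500 mm³ always meets two categories. If the diameter spans the whole nodule, it must exceed 9.85 mm and the pair is III and IV (3-month scan against referral at baseline). If the diameter is that of the non-solid part alone and is below 8 mm, the pair is II and IV (next round against referral).

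**The case against.** **Solid and part-solid nodules are different objects.** Figure 3 deliberately uses different measures for different types: volume for solid, minimal diameter for pleural-based, mean diameter for non-solid. Nothing in the protocol says that equal solid volume must lead to equal action. Read literally, the 100 mm³ example meets only NODCAT II and receives one result. This stands to the extent that the example is not a nodule with two answers. The mismatch remains, because the same figure uses solid volume for part-solid nodules in NODCAT IV and counts a new solid component as positive in GROWCAT C. The wording is also unsteady: NODCAT III speaks of a solid nodule with a non-solid component where the other two lines speak of a partial solid nodule. If such a nodule also counted under the solid-nodule volume line, it would meet II and III together.

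**The overlap above 500 mm³ has a natural reading.** The NODCAT IV line has effect only if it overrides the diameter lines, and sections 7.3 and 8 send every positive finding to a pulmonologist. A reader might call the figure unworkable here, but the documents do not support that. What is missing is a statement of the order, which makes this the weaker half of the point.

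**A line may have been lost in reading the PDF.** This cannot be excluded, but the list shows no visible gap.

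**The effect on the accuracy endpoints is not shown.** A reader might infer that sensitivity or predictive value shifts by a known amount. The documents do not support this: the shift is between negative and indeterminate, the protocol does not say how indeterminate results are counted, and it gives no expected number of cancers or of part-solid nodules.

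**Conclusion.** The point holds for the baseline round. Followed as printed, Figure 3 sends a part-solid nodule with a non-solid component under 8 mm and a solid part of 50 mm³ or more to the next round, about a year later, while a solid nodule of the same volume is rescanned after 3 months. Under the whole-nodule reading with spheres this covers solid parts from 50 to just under 268 mm³, 48% of the band. If the diameter is that of the non-solid part alone, it covers 50–500 mm³. These are shares of a volume range, not of nodules or subjects.

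A reader might extend the negative-versus-indeterminate split to the whole trial. The figure does not support that. For new nodules in round 2 only the timing differs, and the round 4 column, where NODCAT II is again negative, is not reached in a two-round trial.

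The missing order of precedence above 500 mm³ is a secondary point. The number of subjects affected and the effect on sensitivity, predictive value and specificity cannot be determined from the protocol. The primary smoking endpoint is unaffected. The correction should still be made, because the figure decides what a subject is told and when the next scan takes place.

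**What to change.** The sponsor and the study radiologists should:

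1. Reconcile the part-solid lines of NODCAT II, III and IV with each other, with the solid-nodule volume bands and with the GROWCAT C line on new solid components. Where the difference between nodule types is intended, the figure should say so.
2. State whether the 8 mm diameter refers to the whole nodule or to the non-solid component alone, and use one term for part-solid nodules throughout.
3. State which category governs when a nodule meets two.
4. Use the same reconciled classification for the result letter and for scoring sensitivity, positive predictive value and specificity.

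No threshold or order is proposed here; that is a clinical decision. The cost is a corrected figure with a sentence on precedence, and a re-reading of any part-solid nodules already classified.

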## 8. SCREENING RESULT COMMUNICATION TO THE SUBJECT

The results of screening will be communicated in writing to the participants. The letters of explanation will be issued withing four weeks of performance of the screening study.

The participants with positive finding will be directly referred to a pulmonologist.

The participants with intermediate findings will undergo another LDCT in a scheduled manner (Figure 3).

The letter will include:

1. Statement providing the overall results of the screening (negative, intermediate, or positive).
2. Statement providing further recommended steps on the screening results (timing of next LDCT, or referral)

## 9. QUALITY REQUIREMENTS AND CONTROL MEASURES FOR LDCT

### 9.1 Qualifications of Personnel

#### 9.1.1 Qualifications of Study Physicians

Study physicians participating in the trial should meet the following qualifications:

- Must have a valid, active medical license
- A valid GCP licence
- Understanding of the standard practices for lung cancer diagnostics and smoking cessation

#### 9.1.2 Qualifications of Study Nurses

Study nurses participating in the trial should meet the following qualifications:

- Must have a valid, active medical license
- A valid GCP licence
- Understanding of the standard practices for smoking cessation

### 9.2 CT Equipment Certification and Qualifications

Any imaging equipment or scanner device used to acquire screening images for the study will be certified for use at the time of site qualification.

## 10. Smoking Cessation Application

### 10.1 Cessation Application Description and ePRO questionnaire

Participants randomized to the smoking intervention arm will receive a smartphone application for smoking cessation for six months. The smartphone application will also be offered for use after six months of follow-up for the participants randomized to standard-of-care. The cessation application supports the smokers in cessation process and aids them to retain smoking-free lifestyle. The individuals use the app for goal setting, decision-making, information sharing, and empowerment in smoking cessation and, in overall, managing their health.

### 10.2 Software Development

The developed application is Android and iPhone compatible and administration and database is backed up in a cloud. All of the communications between the mobile app and the supporting backend will be protected by means of an SSL digital certificate on the server, which will provide end-to-end encrypted communications. The application is beta-tested with up to ten users.

